#### Sample size

The future intended purpose of CBA measurement is to ‘rule in’ patients with complex stroke and/or LVO from the suspected stroke population. The sample size calculation is therefore based on the detection of test specificity. ‘Rule in’ is chosen as the test results would be used to redirect individuals to a neuroscience centre for highly specialist care. Suspected stroke patients without a diagnosis of complex stroke or LVO do not need transportation to a neuroscience centre and should be admitted to the nearest local hospital.

Reported frequencies for LVO, large intracerebral haemorrhages and prior territorial stroke are 27%, 3% and 4% respectively amongst the unselected population with suspected stroke. There are no reliable estimates for the frequency of SSAVS in the unselected UK population—it is an uncommon finding and previous cohorts of LVO patients are likely to have included cases with high degrees of symptomatic stenosis without reporting them separately. Therefore, using the above-reported frequencies and a minimum specificity of 70% from the diagnostic test, alpha = 0.05 and beta = 0.1:
One hundred twelve participants would detect a specificity of 85% (95%CI: 70%–100%) for complex stroke (i.e. LVO + SSAVS + LICH + PTS) versus all other outcomes in the suspected stroke population (i.e. small/medium intracerebral haemorrhage + ischaemic stroke without LVO + TIA + mimic condition).
One hundred one participants would detect a specificity of 85% (95%CI: 70%–100%) for ischaemic stroke due to LVO versus all other outcomes in the suspected stroke population (i.e. SSAVS + LICH + PTS + small/medium intracerebral haemorrhage + ischaemic stroke without LVO + TIA + mimic condition).

In terms of sensitivity, the 112 participants would detect sensitivity of 85% (95%CI: 63%–100%) for complex stroke and 85% (95%CI: 61%–100%) for LVO.

As outlined above, some enrolled participants may not provide data for inclusion in the analyses and this lack of data is difficult to estimate. The initial recruitment target is inflated for 10% data exclusion (124 participants) but prospective monitoring of the number of cases which can contribute to the analyses will occur and fewer or additional participants will be sought if required.

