### Statistical analysis

Objective 1: To determine the diagnostic accuracy of CBA measurement performed using the CVS to identify complex stroke (ischaemic stroke with LVO or SSAVS or LICH ≥ 60 ml in volume or PTS) in patients arriving at the hospital with a paramedic assigned diagnosis of suspected acute stroke.

In the recently published work using this technology, a threshold of CBA = 10 was derived as optimal for identification of complex stroke [21]. This threshold will be validated on the data collected in this study and considered acceptable if it results in specificity of at least 80% and sensitivity of at least 70%. These values have been chosen as clinically important and stringent, to allow validation to be conducted. Sensitivity and specificity will be reported with 95% confidence intervals.

However, the population to be recruited in this study may differ from the earlier work (e.g. less time has elapsed since stroke onset). Therefore, the threshold of CBA = 10 may not result in meeting the criteria described above. If this is the case, a new threshold will be estimated. Univariate logistic regression analysis with diagnosis (complex stroke) as the outcome (*y*) and CBA measurement as the explanatory variable (*x*) will be used to construct an empirical receiver operating characteristic (ROC) curve for all possible thresholds. A new threshold will be chosen to maximize specificity while aiming to maintain a clinically acceptable level of sensitivity (70% in this instance). Sensitivity, specificity and ROC area under curve (AUC) (with confidence intervals) will be reported for the chosen threshold.
2.Objective 2: To determine the diagnostic accuracy of CBA measurement performed using the CVS to identify LVO in patients arriving at the hospital with a paramedic assigned diagnosis of suspected acute stroke.

For this objective, analyses as described above for objective 1 will be conducted, i.e. a threshold of CBA = 10 will initially be evaluated but a new threshold may be estimated if CBA = 10 does not result in sensitivity and specificity meeting the stated criteria.
3.Objective 3: To explore key clinical and radiological influences upon the diagnostic accuracy of CBA measurement for complex stroke and LVO.

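### At the shared threshold of CBA 10, the planned 85% sensitivity and specificity for both targets cannot all hold: the plan's own inputs imply an LVO specificity of about 78%, slightly below the 80% rule

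*Protocol article*

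**What the plan says.** All planning values are in the protocol article, Sample size section.

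- Frequencies: "Reported frequencies for LVO, large intracerebral haemorrhages and prior territorial stroke are 27%, 3% and 4% respectively". For symptomatic severe anterior vessel stenosis (SSAVS), "There are no reliable estimates for the frequency of SSAVS in the unselected UK population", and no figure is used.
- Test parameters: "a minimum specificity of 70% from the diagnostic test, alpha = 0.05 and beta = 0.1". Whether alpha is one-sided or two-sided is not stated.
- Complex stroke: "One hundred twelve participants would detect a specificity of 85% (95%CI: 70%–100%) for complex stroke".
- LVO: "One hundred one participants would detect a specificity of 85% (95%CI: 70%–100%) for ischaemic stroke due to LVO versus all other outcomes". The comparator group is listed as "SSAVS + LICH + PTS + small/medium intracerebral haemorrhage + ischaemic stroke without LVO + TIA + mimic condition".
- Sensitivity: "the 112 participants would detect sensitivity of 85% (95%CI: 63%–100%) for complex stroke and 85% (95%CI: 61%–100%) for LVO".

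Under Statistical analysis, Objective 1 accepts CBA 10 if specificity is at least 80% and sensitivity at least 70%. Objective 2 applies the same analysis to LVO: CBA 10 "will initially be evaluated but a new threshold may be estimated if" those criteria are not met. A new threshold would be chosen to maximise specificity while aiming for 70% sensitivity.

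**The concern.** One threshold applied to one cohort gives each patient a single result, positive or negative. Large intracerebral haemorrhage (LICH), prior territorial stroke (PTS) and SSAVS are target conditions under Objective 1, so the plan expects most of these patients to test positive. Under Objective 2 the same patients are controls, and the same positive results become false positives. The LVO calculation nevertheless uses the same 85% specificity as the complex-stroke calculation, as if moving these patients into the control group had no effect.

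The validation of CBA 10 for LVO is at stake. If the device performs as planned for complex stroke, it is more likely than not to miss the 80% specificity rule for LVO, and the analysis may then move to a threshold estimated on the same data. A reader could take that miss as poor device performance when part of it follows from which patients count as controls.

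**Working it through.** **1. Reproducing the plan's sample sizes.** Reference-negative fractions with SSAVS at 0:
- non-complex = 1 − (0.27 + 0.03 + 0.04) = 0.66
- non-LVO = 1 − 0.27 = 0.73

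Take a one-sample exact binomial test of 70% against 85%, one-sided alpha 0.05, power 90%. The smallest number of negatives from which power stays at or above 90% is 73. That gives 73/0.66 = 110.6 and 73/0.73 = 100. With 74 negatives the totals are 112.1 and 101.4. The stated 112 and 101 are therefore reproduced, each on its own, with about 74 negatives. An exact test at 0.025 needs 90 negatives (totals 137 and 124), so the one-sided 5% basis is the one that fits.

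**2. Positivity in LICH and PTS implied by the planned sensitivities.** Complex-stroke sensitivity is a weighted average over LVO and LICH/PTS:

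(0.34 × 0.85 − 0.27 × 0.85) / 0.07 = 0.85

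**3. Implied LVO specificity at the same threshold.**

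(0.66 × 0.85 + 0.07 × 0.15) / 0.73 = 0.5715 / 0.73 = **78.3%**

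**4. Dependence on the inputs.**

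| Change from the base case | Implied LVO specificity |
|---|---|
| LICH/PTS positivity 100% | 76.8% |
| LICH/PTS positivity 93% | 77.5% |
| LICH/PTS positivity 70% | 79.7% |
| LICH/PTS positivity 50% | 81.6% |
| SSAVS 1% (assumed; taken from the non-complex 66%, 85% positive) | 77.3% |
| SSAVS 5% (assumed; same basis) | 73.5% |
| Complex-stroke specificity 87% | 80.1% |
| Preliminary accuracy from the Background (specificity 92%, sensitivity 93%) | 83.8% |

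To reach 80% with complex-stroke specificity at 85%, LICH/PTS positivity must be at most 1 − (0.80 × 0.73 − 0.66 × 0.85)/0.07 = 67%. With 85% positivity, complex-stroke specificity must be at least (0.80 × 0.73 − 0.07 × 0.15)/0.66 = 86.9%.

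**5. Consequences if true LVO specificity is 78.3%** (exact binomial, one-sided 5% against 70%):

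| Participants | Non-LVO | Critical count | Power at 85% | Power at 78.3% |
|---|---|---|---|---|
| 101 | 74 | 59 | 92% | 45% |
| 112 | 82 | 65 | 94% | 48% |

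An observed specificity of at least 80% needs 66 of 82. The probability is 37% at a true 78.3%, against 90% at a true 85%. If the control mix is fixed at 74 non-complex and 8 LICH/PTS instead of left random, it is 34%.

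**The case against.** **The two specificities need not conflict.** A reader might infer that 85% for complex stroke and 85% for LVO are incompatible in themselves. They are not. Both hold if only 15% of LICH/PTS patients test positive. Complex-stroke sensitivity is then (0.27 × 0.85 + 0.07 × 0.15)/0.34 = 70.6%, which still meets the 70% rule. The conflict appears only when the planned 85% sensitivities are added. This objection stands and limits the point to the four values taken together.

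**There is no arithmetic error in 112 or 101.** Each reproduces, and each can be read as a detectable alternative for its own calculation, not a joint forecast. With 74 negatives and a true 85%, power is indeed above 90%. This also stands: the fault is that the assumptions were not reconciled across objectives.

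**Objective 2 is not set up to fail.** A reader might infer that it is. The expected shortfall is 1.7 percentage points, and the 80% rule names no confidence limit, so it is read here as applying to the point estimate. It would be met in roughly one study in three. The preliminary accuracy would give 83.8%, although the Background itself says that sample did not represent all suspected stroke. A miss is also provided for: an LVO-specific threshold may be estimated that gives up sensitivity for specificity, and the 85% is not expressly tied to CBA 10.

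What remains is that the plan evaluates CBA 10 first for both targets. On its own planning values, LVO specificity there is not 85%.

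**Conclusion.** The point holds as an inconsistency between planning assumptions. With 85% sensitivity for both targets, 85% specificity for complex stroke and the stated frequencies, LVO specificity at CBA 10 is about 78%, not 85%, and so slightly below the 80% rule. The rule would be met in about 37% of studies with 82 non-LVO participants. Power to exclude 70% would be about 45% (101 participants) or 48% (112), not 90%.

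This rests on a shared threshold, on SSAVS taken as 0 (any assumed positive frequency, with those patients testing positive as planned, lowers the figure) and on a one-sided 5% exact test, inferred because it reproduces the stated sizes. The result is sensitive: complex-stroke specificity of about 87%, or LICH/PTS positivity of 67% or less, would bring LVO specificity to 80%. Objective 1 and the enrolment target, which rests on 112, are unaffected.

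**What to change.** Keep the enrolment target of 124 and make two changes.

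1. **Sample size, LVO sentence.** Restate it with the derived figure, for example: *If CBA 10 gives 85% sensitivity and specificity for complex stroke and 85% sensitivity for LVO, the expected LVO specificity is about 78% (SSAVS taken as 0), depending on positivity in LICH, PTS and SSAVS and on complex-stroke specificity; with 112 participants, about 82 of them without LVO, power to exclude 70% is about 48% (one-sided 5% exact).* Alternatively, keep 101 as a stand-alone calculation and state that 85% for LVO is not expected at the same threshold as 85% sensitivity and specificity for complex stroke.
2. **Objective 2 analysis.** Keep the 80% criterion against all other outcomes, and pre-specify that LVO specificity is also reported separately in non-complex controls and in SSAVS/LICH/PTS controls. A miss caused by the control mix can then be recognised as such. Moving the criterion itself to LVO versus non-complex patients is not recommended, because it would change the Objective 2 target and make the bar easier.

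The cost is a less favourable stated figure for LVO and a small additional tabulation. No new data or participants are needed.

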### Study monitoring, quality control and quality assurance

The Chief Investigator will have overall responsibility for study conduct. The local Principal Investigator will be responsible for the day-to-day study conduct at the NHS site. The study will be managed by a coordinating centre based at Newcastle University Stroke Research Group who will provide training and day-to-day support for the NHS site. Quality control will be maintained through adherence to Newcastle Biomedicine Clinical Research Platform SOPs, the study protocol and research governance regulations. The study may be subject to inspection and audit by Newcastle upon Tyne Hospitals NHS Foundation Trust under their remit as sponsor.

### Dissemination of results

The study will be presented at national and international conferences and reported in peer-reviewed journals. Reports will be written for the study funder, sponsor and regulatory bodies. A lay summary of the results will be available for study participants.

## Discussion

There is substantial high-quality evidence that early access to thrombolysis, thrombectomy and specialist care improve stroke outcomes. However, stratification of patients with suspected stroke is challenging and this can lead to delays to care. Cerebral Bioimpedance Asymmetry measurement using the Cerebrotech Visor™ System may enable rapid identification of certain stroke types that benefit from time-critical treatment. In particular, a quick and portable test for LVO could significantly improve access to thrombectomy with subsequent improved outcome improved outcome from this stroke type. This study will provide data about the diagnostic accuracy of CBA measurement for LVO and other types of complex stroke.

### Study status

At the time of submission of this manuscript, the study is in setup. Recruitment is scheduled to commence in October 2019. Protocol version 3 dated 11th May 2019 was used to prepare this manuscript.

## Data Availability

Not applicable.

## Abbreviations

ASPECTS: Alberta Stroke Program Early CT Score AUC Area under curve AVPU Alert Voice Pain Unresponsive CBA Cerebral Bioimpedance Asymmetry CT Computerised tomography CVS Cerebrotech Visor™ System HASU Hyperacute stroke unit ISRCTN International Standard Randomised Controlled Trials Number LICH Large volume intracerebral haemorrhage LVO Large vessel occlusion MRI Magnetic resonance imaging NHS National Health Service NIHSS National Institute of Health Stroke Scale PTS Prior territorial stroke ROC Receiver Operating Characteristic SSAVS Symptomatic severe anterior vessel stenosis STARD Standards for the Reporting of Diagnostic accuracy studies TIA Transient ischaemic attack
